### Cost-Effectiveness Analysis

The CEA will measure cost in monetary units of DHVs and ELs. The effectiveness of the study is measure by the outcomes in number of teeth saved and the ECOHIS score at the 2-year follow-up. CEA assesses the cost of the study through the use of the ICER [8,24,25] and is defined as the ratio of the difference in costs divided by the difference in outcomes. The ICER for this study will be generated by calculating the difference in cost for dental treatment between the intervention group and the control group, divided by the difference in outcomes between the intervention group and the control group (ie, the number of new carious teeth and ECOHIS scores) [8,24,25]. Based on the data collected, the outcome measure for OHRQoL is only from the ECOHIS questionnaire, therefore this study focuses on CEA as a procedure to decide the most cost-effective way to achieve the objectives [11]. Discounting and sensitivity analysis are not conducted because the study does not perform any projection of future years and the cost data of this study is the real-world cost data [14].

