### Sample Size and Randomization

It is estimated that there will be a 5% of incidence of caries in the intervention group during the follow-up, compared with 20% in the control group. This is based on the findings of a study conducted in 2015 by Koh et al that reported a 4% of incidence of caries in the intervention group and 39% in the control group [11]. Using a statistical software, Epi info 7 (Center for Disease Control and Prevention, USA, 2015), a sample size calculation was conducted and a minimum sample of 176 subjects is needed to detect a 15% difference in incidence of caries, with a significance level of 95% and a power of 80% [16]. The researchers decided to aim for doubling the effective sample size to 300 subjects to ensure the effective sample size will be higher than 176 with a high power. After taking sampling error into account and the assumption of a 30% nonresponse rate, followed by the assumption of another 30% of drop-out rate, a total of 600 subjects will be approached to participate in this study.

The kindergartens that agreed to participate will be randomly allocated into either the intervention or control group (1:1) by a random “draw” method. No matching will be done since they all have a similar socioeconomic background. All children aged 5 or 6 years at the participating kindergartens, with parents’ consent to participate, will be included in the study [17].

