### Study Measures

#### Outcome Measures

The primary outcome of this study is the incidence of new caries, measured by the number of children included in the study with new caries, over a period of 2 years. The difference in the number of children with new caries between the intervention and the control groups will be considered as the number of children prevented from developing caries.

The calculated cost of the DHVs used in the intervention will include staff salaries, telephone calls to make appointments, travelling allowances, and administrative costs. The ELs cost is estimated by using the market price to purchase leaflets, staff salaries, telephone calls, travelling allowances, and administration costs. The cost of preventing a child from developing caries will be calculated as the DHVs and ELs cost divided by the number of children prevented from new caries.

The secondary outcome of this study will be the improvement in OHRQoL over a period of 2 years. This is measured by the improvement in the early childhood oral health impact scale (ECOHIS) scores. The difference in the ECOHIS scores between the intervention and the control groups will be considered as the improvement in OHRQoL. The cost of improving the OHRQoL is calculated as the DHVs and ELs cost divided by the improvement in the ECOHIS scores.

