#### Number of New Carious Teeth

An oral examination will be conducted at baseline (before the start of the intervention) and at the end of the 2-year study period by researchers using the NOHPS protocol, which was based on the World Health Organization (WHO) recommendation published in 2013 [19]. The number of new decayed, missing (due to caries), and filled posterior deciduous teeth (dmft), as well as the number of decayed, missing (due to caries), and filled first permanent molars (DMFT) will be recorded. The dmft and DMFT caries assessment is chosen to ensure consistency with the assessment used by the OHD Ministry of Health Malaysia.

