### Data Analysis

Data collected from each visit will be checked for completeness by the research team members before it is keyed into SPSS. All the outcomes measures will be analyzed using the SPSS Program. Descriptive statistics will be used to report new caries teeth, OHRQoL, cost of DHVs and ELs, and the incremental cost effectiveness ratio (ICER) at 6, 12, and 18 months, as well as at the end of the 2-year follow-up period. A *t* test will be used for comparison of means of those parameters between the two groups and over the period of study. Logistic regression analysis will be carried out to test the influence of individual characteristics and on the CEA of the intervention in preventing caries.

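### The trial is sized on children with new caries at 2 years, but the stated t test and ICER count teeth, and effect results are planned at 6, 12 and 18 months, when neither caries nor ECOHIS is measured

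*Protocol article*

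**What the plan says.** **Unit of the primary outcome.** Outcome Measures makes the incidence of new caries primary, "measured by the number of children included in the study with new caries, over a period of 2 years". It also states a contrast, "The difference in the number of children with new caries between the intervention and the control groups will be considered as the number of children" kept free of caries, and a matching ratio, "calculated as the DHVs and ELs cost divided by the number of children prevented from new caries". The first specific objective in the Introduction is likewise framed per child. Sample Size and Randomization assumes that "there will be a 5% of incidence of caries in the intervention group during the follow-up, compared with 20% in the control group" and arrives at a minimum of 176 subjects.

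**Unit of the analysis.** Data Analysis lists new carious teeth, OHRQoL, costs and the ICER, and compares the group means of these by t test. It adds a logistic regression on individual characteristics and the prevention of caries, without naming its dependent variable or a group term. Cost-Effectiveness Analysis says "The effectiveness of the study is measure by the outcomes in number of teeth saved and the ECOHIS score at the 2-year follow-up", and spells out the ICER denominator as new carious teeth and ECOHIS scores.

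**Timing.** Data Analysis plans these results, including the "incremental cost effectiveness ratio (ICER) at 6, 12, and 18 months, as well as at the end of the 2-year follow-up period". The section Number of New Carious Teeth says "An oral examination will be conducted at baseline (before the start of the intervention) and at the end of the 2-year study period". The section on quality of life gives the same two occasions for ECOHIS. At the 6-, 12- and 18-month visits the article lists delivery of the intervention or leaflets and a check of the dental visit diary.

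**The concern.** A trial's main test and headline ratio should use the outcome on which the trial was sized. Here the outcome and sample size sections count children, while the two analysis sections count teeth, and neither unit is marked as the base case. An analyst who follows Data Analysis literally would run a t test on tooth counts, for which the article makes no power claim. An analyst who follows Outcome Measures would report a cost per child prevented; one who follows Cost-Effectiveness Analysis would report a cost per tooth. Both ratios could be produced from the same 2-year examination, and the choice between them could be made after the results are known.

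The timing problem is separate and simpler. An ICER needs an effect difference in its denominator, and the article schedules no effect measurement between baseline and 2 years.

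**Working it through.** **1. Which unit was powered?** Inputs from Sample Size and Randomization: p1 = 0.05, p2 = 0.20, power 80%, and the stated 95% significance level read as alpha 0.05. Two-sided testing is my assumption. With 1:1 allocation, the mean proportion is 0.125.

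- Without continuity correction: n = [1.96·√(2·0.125·0.875) + 0.8416·√(0.05·0.95 + 0.20·0.80)]² / 0.15² = (0.9167 + 0.3834)² / 0.0225 = 75.1, so 76 per arm and 152 in total.
- With continuity correction: n′ = (n/4)·[1 + √(1 + 4/(n·0.15))]² = (75.1/4)·(1 + 1.164)² = 87.9, so 88 per arm and **176 in total**.

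The second line reproduces the article's figure exactly. The other variants tried do not: unpooled variance gives 146, the Kelsey form 154, and one-sided testing 120 (144 with correction). The 176 is therefore a comparison of two proportions of children. The article gives no mean or standard deviation for new carious teeth, so the power of the t test on teeth cannot be calculated.

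**2. Which unit does each section use?**

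| Section | Caries effect unit |
|---|---|
| Introduction, first objective | child |
| Sample Size and Randomization | child (5% against 20%) |
| Outcome Measures | child; cost per child prevented |
| Data Analysis, t test | teeth (means) |
| Data Analysis, logistic regression | not stated |
| Cost-Effectiveness Analysis, effect and ICER | teeth |

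**3. How far apart can the two ratios be?** Take the same cost difference ΔC per child in both ratios. Let mI and mC be the mean number of new carious teeth per affected child in the intervention and control arms. The article gives neither, so the values below are assumptions.

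- Cost per child prevented = ΔC / (0.20 − 0.05) = ΔC / 0.15.
- Cost per tooth saved = ΔC / (0.20·mC − 0.05·mI).
- Cost per tooth ÷ cost per child = 0.15 / (0.20·mC − 0.05·mI), which becomes 1/m if mC = mI = m.

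| mC | mI | Tooth difference per child | Cost per tooth ÷ cost per child |
|---|---|---|---|
| 2 | 2 | 0.40 − 0.10 = 0.30 | 0.50 |
| 3 | 3 | 0.60 − 0.15 = 0.45 | 0.33 |
| 3 | 2 | 0.60 − 0.10 = 0.50 | 0.30 |
| 2 | 3 | 0.40 − 0.15 = 0.25 | 0.60 |

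The range one half to one third needs equal means in the two arms. If the means differ within 2 to 3, the range widens to 0.30 to 0.60.

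**4. What can be computed at each planned time?**

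| Month | Oral examination | ECOHIS | Diary | ICER computable |
|---|---|---|---|---|
| 0 | yes | yes | issued | – |
| 6, 12, 18 | no | no | checked | no |
| 24 | yes | yes | collected | yes |

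Three of the four planned ICER time points have no effect data.

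**The case against.** A reader might infer that the powered endpoint is never compared between arms, or that the first objective is answered only in teeth. The article does not support either reading. Outcome Measures takes the between-group difference in children with new caries and divides a cost by it, which answers the first objective in its own unit. The logistic regression may also use the binary child-level outcome, since its sentence refers to preventing caries. That part of the objection stands. However, Outcome Measures gives a subtraction and not a test, and the regression names neither an outcome nor a group term.

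A reader might also infer that nothing is measured at 6, 12 and 18 months. That is too broad, because the diary is checked then and records visits, procedures and costs. It cannot supply the missing effect data, though. It covers only visits that parents choose to make, it is not the calibrated examination that defines the outcome, and the Introduction itself says most caries in preschool children goes untreated.

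It can fairly be said that an article may leave the exact primary test to a full protocol or SAP. A test simply not named would be no finding. Here the article does name a test and an ICER denominator, and both are in a different unit from its primary outcome. A SAP would have to depart from one section or another.

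Two further points stand. Cost per tooth and cost per child are different quantities, so a numerical gap between them is not in itself bias. And Cost-Effectiveness Analysis ties effectiveness to 2 years, so the unworkable interim results do not damage the 2-year result.

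**Conclusion.** The plan is wrong as written on two counts, both of them contradictions between its own sections.

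First, the primary and powered outcome is a proportion of children, confirmed by exact reproduction of the 176, while the stated t test and ICER denominator use teeth. Following the analysis sections as they stand would not test the powered endpoint, and the article does not say which of two caries ratios is the main one. The selection risk is a possibility that the wording leaves open; nothing suggests that it is intended.

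Second, interim caries, OHRQoL and ICER results at 6, 12 and 18 months cannot be produced from the stated examination schedule. This part rests on no assumption.

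The numerical size of the first count does rest on assumptions: 2 to 3 new carious teeth per affected child, equal in both arms, and the same cost difference in both ratios. It illustrates how much the choice of unit could matter and is not an estimate from the trial.

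**What to change.** - **Cost-Effectiveness Analysis:** make the base-case caries effect the between-arm difference in the proportion of children with at least one new carious tooth at 2 years, in line with Outcome Measures and the sample size. Label the ICER per tooth as secondary.
- **Data Analysis:** replace the t test on teeth as the main caries comparison with the between-arm difference in that proportion, by a logistic model or risk difference with a group term. Because Sample Size and Randomization allocates whole kindergartens, the model should allow for that. State the dependent variable of the logistic regression already planned.
- **Data Analysis, timing:** remove new caries, OHRQoL and the ICER at 6, 12 and 18 months, and limit those reports to cumulative costs.

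The cost is a wording change to the protocol, and to the SAP if there is one. Both units come from the same 2-year examination, so no new data, visits or participants are needed. The change should be dated before the 2-year data are analysed.

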#### Oral Health-Related Quality of Life Improvement

The OHRQoL improvement will be measured using the ECOHIS questionnaire. The ECOHIS questionnaire is a specific instrument developed by Pahel et al in 2007 to assess the perception of parents on OHRQoL of preschool children. It has 13 items, distributed between 2 sections, namely the Child Impact Section and the Family Impact Section. The Child Impact Section has 4 domains (child symptom, function, psychological, and self-image or social interaction); and the Family Impact Section has 2 domains (parent distress and family function). Responses are recorded using a 5-point Likert scale to record how often an event has occurred where 0=never, 1=hardly ever, 2=occasionally, 3=often, 4=very often, and 5=don’t know [20]. The ECOHIS has been validated on a Malaysian population and was found to have high validity (Cronbach alpha=.83) and high reliability (kappa=.95) in assessing the impact of oral disorders or conditions on the quality of life of urban preschool children age 4 to 6 years old as reported by Hashim et al [21].

The ECOHIS questionnaire will be completed by the parents in both the intervention and control groups at baseline and at the end of the 2-year follow-up period. Based on the responses, the ECHOIS score as prescribed by Hashim will be computed. The ECOHIS score at the end of the 2-year follow-up will be used to assess the improvement of OHRQoL of the children in both intervention and control groups.

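### The ICER formula conflicts with the effect and cost measures named beside it, and by itself cannot tell a cost-saving benefit from a cost-raising harm

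*Protocol article*

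**What the plan says.** The Cost-Effectiveness Analysis section describes the same quantities in two ways.

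- Cost: "The CEA will measure cost in monetary units of DHVs and ELs". The ICER, however, is to be obtained by "calculating the difference in cost for dental treatment between the intervention group and the control group", so the formula carries treatment cost and not delivery cost.
- Effect: "The effectiveness of the study is measure by the outcomes in number of teeth saved and the ECOHIS score at the 2-year follow-up". The formula then has the cost difference "divided by the difference in outcomes between the intervention group and the control group (ie, the number of new carious teeth and ECOHIS scores".

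Teeth saved is a benefit; new carious teeth is a harm. The ECOHIS items are coded "0=never, 1=hardly ever, 2=occasionally, 3=often, 4=very often" (Oral Health-Related Quality of Life Improvement), so a higher score also means a worse state, assuming the score rises with the item codes. The section gives the analysis a deciding role: "this study focuses on CEA as a procedure to decide the most cost-effective way to achieve the objectives".

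Other sections add to this. Outcome Measures defines a separate ratio for caries, "calculated as the DHVs and ELs cost divided by the number of children prevented from new caries", and a parallel one for ECOHIS improvement. Data Analysis reports new carious teeth, quality of life and delivery cost next to the ICER, with t tests between groups. The third objective in the Introduction compares treatment cost between groups. Study Design adopts a societal perspective.

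**The concern.** An ICER is normally read as the price of one unit of benefit. Here the denominator counts harm, and numerator and denominator are described in the same group order. A negative cost difference over a negative caries difference is positive, and so is a positive over a positive. The first is the best possible result and the second the worst.

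A treatment-only numerator sharpens the problem. Treatment cost tends to fall when caries falls and rise when it rises, so these two cases are the ones to expect, and the ratio mostly estimates what it costs to treat a carious tooth. That says little about whether home visits are worth their cost, which the formula leaves out. At stake is how the ratio will be read, and whether it answers the study's question.

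**Working it through.** **The plan's own figures.** The protocol states no ICER value. Its effect assumption is 5% against 20% caries incidence (Sample Size and Randomization). With two-sided alpha 0.05, 80% power and equal arms, the two-proportion formula gives 76 per arm (152) without continuity correction and 88 per arm (176) with it. The stated 176 is reproduced, so these incidences can serve as inputs, with 150 per arm from the target of 300.

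**Assumptions not in the documents.** A mean of 2 new carious teeth per affected child; treatment cost c per new carious tooth of 20, 100 or 500 units; extra delivery cost D of the intervention per child of 0, 100 or 400 units (200 in the simulation).

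**New carious teeth per child.** Control: 0.20 × 2 = 0.4. Intervention if it helps: 0.05 × 2 = 0.1. If it harms by the same 15 points: 0.35 × 2 = 0.7. The differences, intervention minus control, are −0.3 and +0.3.

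**Formula as written, treatment cost only.** Ratio = c(Ti − Tc)/(Ti − Tc) = c. At c = 100:

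- help: −30/−0.3 = +100
- harm: +30/+0.3 = +100
- no effect: 0/0, undefined

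**Adding delivery cost, and reversing the denominator.** Numerator = D + c(Ti − Tc).

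| c | D | Over new carious teeth: help | harm | Over teeth saved: help | harm |
|---|---|---|---|---|---|
| 100 | 0 | +100 | +100 | −100 | −100 |
| 20 | 100 | −313 | +353 | +313 | −353 |
| 100 | 100 | −233 | +433 | +233 | −433 |
| 500 | 100 | +167 | +833 | −167 | −833 |

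For example, at c = 100 and D = 100, help is (100 − 30)/−0.3 = −233 and harm is (100 + 30)/0.3 = +433. At c = 500, help is (100 − 150)/−0.3 = +167.

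Three things follow. With treatment cost alone, reversing the denominator turns +c into −c for help and harm alike, so it cures nothing. Adding delivery cost separates them by sign unless treatment savings exceed D. When they do, as in the last row, the sign coincides again under either denominator, so the two differences must also be shown separately.

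**Sampling variation.** 20,000 simulated trials, 150 children per arm, c = 100, no clustering by kindergarten, treatment cost only:

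- All carious teeth treated, unrelated dental cost averaging 20 per child: medians 100 for help (95% range 82 to 118), 100 for no effect (−91 to 295; positive in 94% of trials) and 100 for harm (77 to 122).
- Half treated, unrelated cost averaging 50: medians about 50 in all three; positive in 97.5%, 71% and 95% of trials.

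With D = 200 in the numerator (all teeth treated, unrelated cost 20), the medians separate to about −570 for help and +765 for harm; with no effect the ratio is positive in about 50% of trials.

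**The case against.** The strongest reply is that no order of subtraction is written down. Outcome Measures treats the between-group differences as children spared caries and as improvement, and teeth saved points the same way, so the denominator may be meant as caries averted. That is fair, and the sign is indeed a matter of reading. It does not rescue the formula: with treatment cost alone, help and harm then both give −c.

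It can also be said that every ICER shares its sign across opposite quadrants, and that dominance rules and intervals belong in an analysis plan. True in general. The finding here is the stated formula, which contradicts the effect and cost named in its own section and makes the ambiguous quadrants the expected ones.

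A reader might go further and infer that the ICER is the only basis for a decision, so that a harmful result could pass as a beneficial one. The documents do not support that. Outcome Measures gives two other ratios, Data Analysis compares caries and quality of life directly, and the third objective compares treatment cost. Those two ratios label the difference as benefit in advance, but the separate comparisons would show which way caries moved.

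The simulated percentages may rightly be discounted: the unit costs, treated share and tooth counts are not in the protocol.

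**Conclusion.** The point holds in limited form. The ICER formula disagrees with teeth saved, and with the cost of visits and leaflets, in the same section. Taken literally it gives a positive value both for a cost-saving benefit and for a cost-raising harm. If treatment cost is proportional to new carious teeth, the two values are identical (100 and 100 at c = 100) for any c. The direction is recoverable from other planned results, but not from this ratio.

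Limits:

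- It would be tempting to say that visits with no effect yield the same positive figure. They do not: the true ratio is 0/0, and sample values only centre near the treatment cost per tooth, vary widely and can be negative.
- Equal values need the treatment-only numerator and treatment cost that follows caries. The intervention encourages dental check-ups, so treatment spending could rise while caries falls.
- For ECOHIS, equal values would need treatment cost to follow the score; otherwise only the sign coincides.
- The simulation is illustrative only.

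This should be corrected before analysis, because it changes what the ratio can support.

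**What to change.** In the Cost-Effectiveness Analysis section:

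1. Define effect as control minus intervention: carious teeth averted per child and ECOHIS points reduced. This matches teeth saved and Outcome Measures.
2. Define cost as intervention minus control, and reconcile the two cost descriptions so that the numerator holds visit and leaflet delivery cost as well as treatment cost, in line with the societal perspective.
3. Report the cost difference and the effect difference separately, each with an interval.
4. State the quadrant first (dominant, dominated or neither). Quote an ICER only when the intervention is costlier and better, or cheaper and worse.

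Steps 1 and 2 alone are not enough: at c = 500 and D = 100 the corrected ratio is −167 for help and −833 for harm. Under step 4 these would be reported as dominant and dominated, with no ratio.

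The cost is a few sentences of wording; both kinds of cost and both outcomes are already to be collected. The small downside is that some results will have no single ICER to quote.

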Cost-effectiveness analysis (CEA) is widely used to inform decision-makers about the value of new health programs and interventions. CEA is the most commonly used technique for economic evaluation and it estimates the costs and effects of health interventions and sums up the results in a cost-effectiveness ratio [14].

Given the high prevalence of dental caries in Malaysia, and the availability of effective DHVs and ELs material to support oral health promotion, the rationale of this study is to identify effective and cost-effective behavioral interventions to promote oral health and reduce oral health disparities in the population [1,7,8,12,13]. Health behaviors and lifestyles can influence both the oral and general long-term health of the population which can have economic and social consequences [15]. Furthermore, this is the first reported study of DHVs in Malaysia and an economic evaluation in this area is needed to estimate the value of the outcomes received for the expenditures spent on this intervention.

The aim of this study is to evaluate the cost-effectiveness of DHVs and oral health information in the form of ELs in preventing new caries development in young children, compared to those receiving only ELs over a period of 2 years. The specific objectives are:

To determine the cost of DHVs and ELs for prevention of new caries per child compared to the cost for a child only receiving oral health information through ELs for prevention of new caries after a 2-year follow-up.To determine the cost of DHVs and ELs in improving the oral health-related quality of life (OHRQoL) for one child compared to the cost of only ELs in improving the OHRQoL for one child after a 2-year follow-up.To compare the cost of dental treatment incurred and all associated expenditures among children receiving DHVs and ELs and those receiving only ELs over 2 years.

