#### Costs of Dental Home Visits and Educational Leaflets

The DHVs cost data will include the cost of dental home visitors, telephone calls, administration costs, and travelling costs of dental home visitors. The costs of the dental home visitors will be calculated according to the average salary of a dental nurse; the costs of the telephone calls used to make appointments for DHVs will be estimated according to the fees of prepaid phone number; and the travelling costs of the dental home visitors will be estimated by the average travel allowance per day in the Selangor area. The administration cost will include the costs of paper, stationary, and photocopies used for the informed consent forms and letters to authorities, as well as the training cost for delivering intervention. As the ELs used in the study will be obtained from existing Ministry of Health leaflets which are most relevant to the study objectives, the ELs cost in this study will be estimated by using the market price for purchase of leaflets, staff salaries, telephone calls, travelling allowances, and administration costs.

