#### Costs of Dental Treatment

The cost data for dental treatment incurred by the families will be obtained from the recorded dental visit diary completed by the parents. The dental visit diary will be created to record every dental visit made during the study period and checked by the researchers every six months until the end of the study period. The information recorded in the diary will capture the reason for the dental visit, the type of dental clinic visited, the dental treatment or procedure conducted, the time spent at the dental clinic, the time spent travelling to and from the dental clinic, the total cost of the dental treatment or procedure, the cost of travelling to and from the dental clinic, the person who brought the child to the dental clinic, and the number of parents’ days off used to bring the child to the dental clinic. The use of dental visit diary has been reported to be suitable for self-completion by the parents [22].

The dental visit diary will be created according to an annotated cost questionnaire as proposed and validated by Thompson and Wordsworth for the UK Health Economics Research Unit [22]. It will be translated to Bahasa Malaysia using the forward and backward translation process. It will be pretested to assess its relevance and ease of understanding by the potential participants in the context of the communities included in the study.

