#### Baseline Data

The baseline clinical data for all study participants will be based on the oral examination to be carried out at the kindergarten for all children with the parents’ consent. This examination will be conducted by researchers who have successfully attended the standardization training session. Oral examination will use a disposable mouth mirror. Caries assessment will be based on visual inspection, without invasive probing, and is diagnosed at the cavitation stage. Both primary and permanent teeth will be examined and if a permanent and a primary tooth occupy the same space, then only the status of the permanent tooth will be recorded. Caries assessment will adhere closely to the NOHPS criteria [17], which has been modified in 2013 from the WHO recommendations [21]. It is important to note that the WHO uses alphabets to denote caries status for primary teeth, however, NOHPS protocol uses numeral for both primary and permanent teeth. Hence, in this study, the following coding will be used: Sound teeth=0 (instead of A), Caries=1 (instead of B), Filled with caries=2 (instead of C) and Filled no caries=3 (instead of D). The teeth examination will begin from upper right to upper left and lower left to lower right quadrant and a tooth will be considered present when any part of it is visible [19,23]. No radiographs will be taken, and no treatment will be provided. Children who have been assessed with obvious caries will be advised to visit a dental clinic for further assessment and for treatment if necessary.

Baseline DHVs will be carried out and the parents in both the intervention and control groups will receive the ECOHIS questionnaire and a dental visit diary. The baseline ECOHIS questionnaire will be filled by the parents during the visit and returned to the researchers. The dental visit diary will be maintained by the parents and the research team will check the diary every 6 months. Parents will be informed to complete the diary every time their children visit the dental clinic.

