#### Follow-Up 6-Monthly Visits

Follow-up visits will be made every 6 months at the 6th, 12th, 18th month of the study period to the homes of both the groups. The parents in intervention group will receive DHVs and ELs by the dental home visitors, while those in the control group will receive only ELs to be delivered by the dental home visitors. The researchers will check the dental visit diary from both groups at each 6-month visit.

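### Discounting is ruled out because nothing is projected, but costs and effects run over two years; the reason does not support the rule, and the numerical effect is small.

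*Protocol article*

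**What the plan says.** The Cost-Effectiveness Analysis section fixes the rule and gives a reason: "Discounting and sensitivity analysis are not conducted because the study does not perform any projection of future years". The same sentence gives a second reason: "the cost data of this study is the real-world cost data".

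Other sections set the timing:

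- **Horizon.** The aim in the Introduction is a comparison of home visits plus leaflets, "compared to those receiving only ELs over a period of 2 years".
- **Start.** Under Baseline Data: "Baseline DHVs will be carried out and the parents in both the intervention and control groups will receive the ECOHIS questionnaire".
- **Later contacts.** Under Follow-Up 6-Monthly Visits: "Follow-up visits will be made every 6 months at the 6th, 12th, 18th month of the study period". These go to both groups.
- **Treatment costs.** Under Costs of Dental Treatment, parents keep a diary to "record every dental visit made during the study period and checked by the researchers every six months until the end of the study period".
- **Early costs.** Under Costs of Dental Home Visits and Educational Leaflets, administration covers consent forms and letters, "as well as the training cost for delivering intervention".
- **Effect.** The 2-Year Follow-Up Data section places the second dental examination and the closing quality-of-life questionnaire at month 24.

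The article defines two ratios. Outcome Measures divides the programme cost (visits and leaflets) by the number of children kept free of new caries, or by the gain in ECOHIS score. Cost-Effectiveness Analysis divides the between-group difference in dental treatment cost by the difference in new carious teeth or ECOHIS score.

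**The concern.** Discounting puts amounts that arise in different years on one time base. It applies to observed amounts as much as to forecast ones. A study that projects nothing but collects costs over two years still has amounts on two time bases, and real-world collection does not alter their dates. The rule therefore rests on reasons that do not support it. This is a stated rule with a wrong rationale, not a detail left to a fuller document.

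At stake is the meaning of the summed cost and of each ratio: second-year amounts carry the same weight as first-year amounts. The quoted sentence also rules out sensitivity analysis. That is a separate matter, and this point concerns discounting only.

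**Working it through.** The article states no discount rate, cost amount or split of costs by year, so it has no figure of its own to reproduce here. The rate r, the second-year cost share s and the second-year effect share e are assumptions.

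**1. Timing of delivery contacts.** From Baseline Data and Follow-Up 6-Monthly Visits, contacts fall at months 0, 6, 12 and 18. Two of the four fall at or after month 12. Month 12 lies on the boundary: assigned to year 1, it leaves one of four in year 2. So s for contacts is 0.50 or 0.25.

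**2. Total cost.** With year 1 at face value and year 2 discounted by one year, the cost factor is C = (1 − s) + s/(1 + r). The fall from the face-value total is 1 − C:

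| s | r = 3% | r = 5% |
|---|---|---|
| 0.25 | 0.7% | 1.2% |
| 0.50 | 1.5% | 2.4% |
| 0.75 | 2.2% | 3.6% |

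Dating four equal contacts exactly, the mean of (1 + r)^−t at t = 0, 0.5, 1 and 1.5 years gives falls of 2.2% (3%) and 3.6% (5%).

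**3. The defined ratios.** With effect factor E = (1 − e) + e/(1 + r), each ratio is multiplied by C/E. If all effects are placed in year 2 (e = 1), this reduces to 1 + (1 − s)r.

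Programme-cost ratio (Outcome Measures), s = 0.50:
- e = 1: 1 + 0.5r = 1.015 (3%), 1.025 (5%), so +1.5% and +2.5%.
- e = 0.5 (effects spread evenly): C = E, so no change.
- Costs discounted, effects not: 0.9854 and 0.9762, so −1.5% and −2.4%.

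Treatment-cost ratio (Cost-Effectiveness Analysis), with an assumed 80% of the cost difference in year 2:
- e = 1: 1 + 0.2r = 1.006 and 1.010, so +0.6% and +1.0%.
- e = 0.5: 0.9767/0.9854 = 0.991 and 0.9619/0.9762 = 0.985, so −0.9% and −1.5%.

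One corner lies outside this range. With month 12 counted in year 1 (s = 0.25) and e = 1, the programme-cost ratio changes by 1 + 0.75r, that is +2.25% and +3.75%.

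**4. Netting savings against programme cost (illustrative).** Neither defined ratio does this. Suppose treatment savings equal a fraction k of programme cost, with s = 0.50 for programme cost and 80% of savings in year 2. Net cost is then C(0.5) − k·C(0.8), against 1 − k at face value:
- k = 0.5: 0.9854 − 0.5 × 0.9767 = 0.4971 against 0.50, so −0.6% (−1.0% at 5%).
- k = 0.8: 0.9854 − 0.8 × 0.9767 = 0.2041 against 0.20, so +2.0% (+3.3% at 5%).
- The sign changes at k = 0.5/0.8 = 62.5%, at any rate.

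**The case against.** The strongest reply is that over two years the omission hardly matters, and that an undiscounted analysis could be defended on that ground. Much of this stands. The shifts are a few per cent at most on the ratios defined, they vanish if costs and effects share the same timing, and no conclusion is shown to change. But a short horizon is not the ground the article gives. It relies on the absence of projection and on real-world data, and neither supports the rule.

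Three stronger readings are tempting, and the documents support none of them.

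- **Half of the trial's costs fall in year 2.** A reader might infer this from the visit schedule. It is only a count of delivery contacts, with month 12 on the boundary. Training and consent costs fall mainly early, and the timing of treatment costs is unknown.
- **Face-value costs are known to favour the home visits.** One might argue that programme costs come first and savings later. On the assumptions in step 4, discounting raises net cost only if savings exceed 62.5% of programme cost; below that it lowers it.
- **The ratio is off by 5–16%.** Such figures arise if 80–90% of programme cost is offset and all effects are placed in year 2: 2.0% on net cost becomes 1.0204 × 1.03 = 1.051 at 3%, and a 90% offset at 5% gives about 16%. They need a netted numerator that neither ratio writes out, and assumed savings that nearly cancel programme cost.

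Placing all effects in year 2 is also an upper case. Caries incidence accrues over both years; month 24 is only when it is examined.

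**Conclusion.** The rationale is wrong, and the rule built on it leaves second-year amounts at face value. The consequence is minor. At assumed rates of 3–5%, the discounted total cost is about 0.7–3.6% lower for second-year shares of 25–75%. The defined ratios move by about 0–2.5% in size with half the programme cost, or 80% of the treatment-cost difference, in year 2; the month-12 corner case reaches 3.75%. The direction is not fixed: it depends on when costs, savings and effects fall, and on whether effects are discounted. Larger shifts arise only if savings are netted against programme cost and nearly cancel it, which is illustration and not something the documents show. All rates and shares are assumptions; only the 2-year horizon, the contact schedule, the diary period and the month-24 measurement come from the article.

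**What to change.** In Cost-Effectiveness Analysis, delete the no-projection and real-world-data rationale as it applies to discounting. State instead that costs arising after month 12, and the effects, are discounted at one named annual rate (for example 3%), with undiscounted (0%) and 5% results alongside. Say to which year the month-12 contact belongs and how effects observed at month 24 are dated.

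The cost is one extra line of calculation and a slightly different stated ratio. Contacts are already scheduled. The diary fields listed in the article do not include the date of each dental visit, but the diary is "checked by the researchers every six months until the end of the study period", so treatment costs can be dated roughly to a half-year without new data collection. The 0% result keeps the analysis as now planned in view.
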